#### Primary analysis

Boosters will be compared to two primary doses with at least 175 days prior to the onset but with no booster dose recorded. The comparison will be within those with the same priming vaccine.

#### Secondary analysis

- Boosters compared to unvaccinated individuals (this will also allow assessment of residual effectiveness of 2 doses).
- Boosters compared to a period shortly after a booster dose was received-The period will be selected after plotting the data on case and control numbers after the booster dose and to avoid vaccine reactogenicity which may affect the case-control ratio

#### 4. Limitations

- Imperfect sensitivity PCR testing could cause misclassification of both cases and controls
- Many individuals will also have been previously infected so the VE measured is in the context of a population where many have already had natural exposure
- Unaccounted residual confounding
- The unvaccinated as a comparator is most susceptible to residual confounding as the totally unvaccinated population may differ in many ways to those who have had vaccine doses, many of which may lead to underestimation of VE. If a period shortly after dose 3 can be identified this should have the least issues with confounding.

#### 5. Reporting

Reports will be produced for JCVI and made available on MEDRXIV before preparation for publication in a peer reviewed journal.

All reports will also be published here: <https://www.gov.uk/guidance/monitoring-reports-of-the-effectiveness-of-covid-19-vaccination>

## 6. Additional exploratory analyses

**15/11/2021:** Additional analysis planned to assess VE according to the interval between the first and second dose. Intervals to be determined after examination of the distribution of intervals by age and vaccine. Comparison will be of absolute VE against unvaccinated by interval and of odds of testing positive 14 or more days after a booster in those with shorter intervals compared to longer intervals.

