#### Vaccination data- The National Immunisation Management System (NIMS)

Booster doses will be identified as being a third dose 175 days or more after a second dose and given after 13th September 2021.

Only individuals who are unvaccinated at the time of onset or who have had two or three doses of vaccine at the time of onset will be included. In addition, there must be an interval of at least 175 days from dose2 to dose3 or from dose 2 to onset. Individuals with a mix of vaccines in their primary schedule or less than 19 days between their first and second dose will be excluded.

Therefore, a booster is recognised as a booster if given at least 175 days after a second dose.

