### 3.9. Statistical analysis

We will use a test-negative case-control design to estimate vaccine effectiveness of a booster dose of BNT162b2 vaccine against PCR-confirmed symptomatic disease, hospitalisation and death. Analysis will be by logistic regression with the PCR test result as the dependent variable where those

testing positive are cases and those testing negative controls. Vaccination status will include as an independent variable and effectiveness defined as 1- odds of vaccination in cases/odds of vaccination in controls. Estimates will be reported with 95% confidence intervals. Analyses will stratified by which primary doses had been received.

Vaccine effectiveness will be adjusted in logistic regression models for:

- age (5 year bands)
- sex
- index of multiple deprivation (quintile)
- ethnic group
- care home residence status
- geographic region (nhs region)
- period (calendar week of onset)
- health and social care worker status
- clinical risk group status
- clinically extremely vulnerable
- severely immunosuppressed
- previously testing positive

These factors will all be considered potential confounders so will be included in all models.

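### The exploratory comparison by dose 1-2 interval, pooled from day 14 after the booster, can be confounded by time since booster, in a direction the protocol does not settle

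*Protocol*

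**What the plan says.** Protocol section 6, in an entry dated 15/11/2021, adds an analysis by the interval between the first and second dose. It has two contrasts. One is the "odds of testing positive 14 or more days after a booster in those with shorter intervals compared to longer intervals". For the other, "Comparison will be of absolute VE against unvaccinated by interval", no post-booster band is given. The cut-offs are left open: "Intervals to be determined after examination of the distribution of intervals by age and vaccine".

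Section 3.9 lists the adjustment variables and states: "These factors will all be considered potential confounders so will be included in all models". The list has age in 5-year bands, calendar week of onset, care home, worker and clinical risk variables, and previous positive test. Time since booster, booster date and the dates of doses 1 and 2 are not on it. Section 3.9 also says: "Analyses will stratified by which primary doses had been received".

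Booster timing is tied to dose 2. Section 1 reports a recommendation of no earlier than 6 months after the primary course, and the vaccination data part of section 3.2 says: "Booster doses will be identified as being a third dose 175 days or more after a second dose".

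Elsewhere the protocol treats time since booster as possibly important. Section 3.5 has bands of 14-34, 35-69 and 70+ days for a BNT162b2 primary course with a BNT162b2 booster, and section 7 explains that the bands let potential waning be assessed. For ChAdOx1-S followed by BNT162b2, section 3.5 stops at 35-69 days. For both Moderna-booster groups it uses a single category from day 14.

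**The concern.** In the main models, time since booster is part of the exposure definition, so it need not be a covariate as well. In the section 6 contrast the exposure is the dose 1-2 interval, everyone is boosted, and the whole period from day 14 is one category. Time since booster is then an ordinary potential confounder. It may affect the odds of testing positive, and it may differ between interval groups because the date of dose 2 governs when a booster can be given.

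Adjusting for week of onset does not remove this. Within an onset week, time since booster is the onset date minus the booster date, so any difference in booster date between the groups enters the contrast in full.

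At stake is the reading of the result. Section 5 sends reports to JCVI and to publication. An odds ratio away from 1 could be taken as a lasting effect of the primary schedule when part or all of it reflects how recently each group was boosted.

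**Working it through.** The protocol states no effect size, power or sample size for this analysis, so there is no figure to reproduce. The check uses its dates, then an illustrative simulation.

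**1. Width of the pooled window.** Boosters began on 14 September 2021 (section 1).
- To 15/11/2021: 16 + 31 + 15 = 62 days at most, so the window spans days 14-62.
- To 06/12/2021: 16 + 31 + 30 + 6 = 83 days at most, so it spans days 14-83 and crosses all three bands.

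**2. Possible shift in eligibility.** The minimum dose 1-2 interval is 19 days (section 3.2). Take 8, 10 or 12 weeks as the longer interval (an assumption). For the same dose 1 date, dose 2 and hence eligibility come earlier by 56 - 19 = 37, 70 - 19 = 51 or 84 - 19 = 65 days. The programme start compresses part of this: anyone with dose 2 by 23 March 2021 (14 September less 175 days) already met the 175-day rule on the first day.

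**3. How much follow-up can lie at 70+ days by 06/12/2021.** Assume onsets spread evenly over days 14-83.
- Everyone boosted on day one: 14/70 = 20%.
- Booster uptake also even: (1 + ... + 14)/(1 + ... + 70) = 105/2485, about 4%.

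**4. Simulation with no true interval effect.** All inputs in this step are assumptions.
- 400,000 people per scenario, half of them short-interval.
- Long-interval eligibility uniform from day -20 to day 70 relative to 14 September; short-interval eligibility shifted.
- Booster given at eligibility, or at programme start if later, plus an exponential delay with mean 10 days.
- Onset uniform over days 14-83; only those at least 14 days after the booster kept.
- Odds relative to two doses in the bands 14-34/35-69/70+: none 0.15/0.15/0.15, slight 0.12/0.14/0.17, moderate 0.12/0.18/0.25, strong 0.10/0.20/0.35.
- Logistic regression of test result on short versus long interval and onset week, fitted without and with the three bands.

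Short/long odds ratio adjusted for onset week only (true value 1.00):

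| Short-interval eligibility | None | Slight | Moderate | Strong |
|---|---|---|---|---|
| Same | 1.03 | 0.99 | 1.00 | 1.01 |
| 20 days earlier | 1.01 | 1.01 | 1.03 | 1.08 |
| 40 days earlier | 1.01 | 1.03 | 1.11 | 1.16 |
| 65 days earlier | 1.02 | 1.05 | 1.15 | 1.26 |
| 40 days later | 1.01 | 0.94 | 0.83 | 0.70 |

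With the bands added, every cell lies between 0.98 and 1.03. The rows and columns with no bias by construction range from 0.99 to 1.03, which shows the simulation noise, so the smallest entries cannot be told from 1.

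The 65-day shift moved mean time since booster by only about 5 to 7 days (for example 44 against 39), because the programme start absorbs much of it. The 40-day delay moved it by about 10 to 11 days (28 against 38 or 39), which is why that row departs further from 1.

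**The case against.** The strongest reply has four parts.

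**Silence is not a decision.** Section 6 is a short exploratory note with no model of its own. Section 3.9 says that the listed factors go into all models, not that others are barred, and a separate analysis plan could add the term. This is fair as far as it goes. But the protocol does state the contrast, with its pooled window, and the covariates for every model. Followed as written, these leave the confounder in.

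**Direction.** A reader might infer that shorter-interval people were boosted earlier and so carry more waning. The documents do not support that as a fact. It follows only for similar dose 1 dates, which the planned comparison does not hold fixed, and no booster dates by interval are given. If short intervals belong to people vaccinated later, the bias reverses. This part of the objection stands in full.

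**Size.** A reader might reach a larger figure by assuming band mixes directly. With odds of 0.10/0.14/0.20 and mixes of 30/40/30% (short) and 70/28/2% (long), the ratio is (0.030 + 0.056 + 0.060)/(0.070 + 0.0392 + 0.004) = 0.146/0.1132 = 1.29. But 30% at 70+ days exceeds even the 20% reached if everyone were boosted on day one, with onsets to 06/12/2021, and the sum ignores the adjustment for onset week. Later repeats, planned about every 3 weeks, could hold more follow-up at 70+ days, but the documents give no basis for 30%.

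**Partial protection.** Stratification by primary vaccine and adjustment for age, worker status, care home and clinical risk stand in for part of the roll-out order, and section 4 admits residual confounding. These may reduce the difference in booster dates between the groups. Nothing in the protocol shows that they remove it.

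**Conclusion.** The point holds as a possible bias in one exploratory contrast. The window from day 14 is pooled, booster timing depends on dose 2, and neither time since booster nor booster date is among the stated covariates.

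Under the assumed waning, the spurious odds ratio is about 1.01 to 1.26 if the short-interval group becomes eligible 20 to 65 days earlier, and 0.70 to 0.94 if 40 days later. It is about 1.0 with no waning, which the protocol itself calls only potential. These figures rest on assumed waning, eligibility and uptake patterns, and the simulation adjusts for onset week alone. Its shifts are best read as what remains after the other covariates.

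The sign is not known from the documents, but an unknown sign is still a reason to adjust. No primary or secondary objective depends on this analysis, so those VE estimates are unaffected. This is a cheap improvement, not a flaw in the main study.

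**What to change.** In section 6, state that the post-booster interval comparison includes time since booster in addition to the section 3.9 covariates. A spline or continuous term serves all vaccine combinations. The bands 14-34, 35-69 and 70+ days can be used where numbers allow, bearing in mind that section 3.5 defines all three only for BNT162b2 primary with BNT162b2 booster. Report post-booster absolute VE by interval within the same time-since-booster bands where numbers allow.

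Tabulating time since booster by interval group would also show whether the groups differ and in which direction.

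No new data are needed, since booster and onset dates already define the exposure groups. The cost is somewhat wider confidence intervals, and sparse cells in some vaccine combinations if results are split by band.

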## 7. Changes to the analysis plan between version 2.1 (the final version before the first booster analysis) and 2.2 (current version)

| Change                                                                            | date       | Reason                                                                                                                                                              |
|-----------------------------------------------------------------------------------|------------|---------------------------------------------------------------------------------------------------------------------------------------------------------------------|
| Addition of 18-49 analysis                                                        | 06/12/2021 | This age group was added to general recommendation for boosting                                                                                                     |
| Maximum of 1 test negative in the follow-up period                                | 06/12/2021 | As the booster period is quite short using up to 4 random negatives is not necessary and using 1 helps ensure independence.                                         |
| Addition of post booster intervals of 14-34,35-69 and 70+ days post vaccination   | 06/12/2021 | More time has now passed to allow potential waning to be assessed.                                                                                                  |
| Change from 140+ days to 175+ days as the comparator follow-up period post dose 2 | 06/12/2021 | The vast majority of boosters given at the time of the study were from 175+ days so this represents a better estimate of the waned post dose 2 level of protection. |

